# 3.14 Morbidity surveillance during the rainy season

Study subjects will be followed throughout the rainy season. Mothers/guardians will be encouraged to take their child to the RVH OPD clinic or the health centre identified as being closest to their home at any time after discharge if the child becomes unwell. Project staff will be based at each of these health centres, initially to identify children in the trial and to ensure that they are seen, properly investigated and treated promptly by health centre staff. At each visit axillary temperature will be recorded using a digital thermometer. A dipstick for diagnosis of malaria will be used to guide treatment if fever (axillary temperature of  37.5°C) or history of fever within the previous 48 hours is present. In addition, a thick blood smear for malaria parasites will be collected for subsequent confirmation of the diagnosis. Filter paper sample to test for S/P resistance will be collected from all malaria cases detected during morbidity surveillance. Study subjects with documented fever (axillary temperature of  37.5°C) or history of recent fever and malaria parasitaemia will be treated with S/P and chloroquine. The treatment of study subjects seen at the health centres will be the carried out by health centre staff in accordance with national guidelines. Study patients needing admission will be referred to RVH paediatric unit or the MRC ward. The Health centre ambulance will be used to transfer study patients referred for admission but if this is not available, the field worker will arrange for the use of MRC transport as soon as possible. Study children admitted to the RVH or MRC hospital will be fully documented.

# 3.15 End of malaria transmission season cross-sectional survey

Children enrolled in the study will be seen at the OPD clinic at the end of malaria transmission season for examination by a study physician and a finger-prick blood sample will be obtained for preparation of thick blood smear and determination of haemoglobin concentration. A standardized questionnaire will be administered to the parents/guardians of the study subject, to collect information regarding illness that had occurred since the last visit, symptoms experienced, use of healthcare facilities and use of medicines. Information on the use of bednets will be collected again at this visit.

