3.5 Screening process and enrolment

All children in the right age group who present to the ward/OPD will have their haemoglobin concentration measured and blood film examined for the presence of malaria parasite. Children with a haemoglobin concentration of less than 7 g/dL will be offered assessment by a project doctor. If assessment is permitted, and the patient fulfils the entry criteria, then written consent will be sought from the parent/guardian. A screening record will be maintained to log all patients who are considered as potential patients but who are excluded. The study will be explained in the parents/ guardians’ preferred language, and written informed consent will be obtained on approved forms.

On entry into the trial a detailed clinical history, drug history, family history and information on bednet usage and impregnation will be obtained. The study physician will examine the child, document nutritional status and record the findings in a case report form. In addition, a detailed address will be obtained. Each study child will be provided with a photo ID card to facilitate identification at each contact.

A5-ml baseline blood sample will be obtained from the first 142 patients seen at the Royal Victoria Teaching Hospital or MRC Clinic for determination of the following:

- Hb, red cell indices, white cell and platelet count (Coulter counter)
- Reticulocyte count
- Markers of iron status (serum iron and ferritin) (first 100 children)
- Sickling test and, if positive, haemoglobin electrophoresis
- Stool examination for hookworm and other parasites (first 100 children)

Other investigations such as chest x-ray and urine examinations will be carried out as clinically indicated. Whenever possible the cause of the anaemia will be determined

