3.10 Home visit

As soon as possible after discharge from hospital, patients will be visited at home by a project field worker to collect information on social economic and environmental risk factors that may predisposes an individual child to develop severe anaemia. A housing survey will be conducted during this visit to determine possible risk factors for malaria which might act as confounders in determination of the primary trial end-point. Field workers will interview the parents/guardians of study subject to record characteristics about the house that might influence mosquito biting behaviour. These items will include building material, an evaluation of the presence of eaves, impregnation and condition of bed nets. During the visit, parents will be encouraged to protect the study child with a bed net.

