# 3.16 Dry season follow-up

At the end of the dry season study subjects will be visited once. During this visit, a questionnaire will be administered to document morbidity and mortality. Children admitted to

hospital with severe anaemia may be at increased of death if they develop another disease before their haemoglobin has returned to the normal range. Therefore it is important to document the morbidity and mortality pattern in these children over a period of several months after their discharge from hospital.

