# 3.17 Surveillance for overall and cause specific mortality

Deaths will be investigated using the post-mortem questionnaire techniques and cause of death established wherever possible.

3.18 Study end-points:

Primary end-points

- Proportion of children with haemoglobin concentration of less than 7g/dL at the end of the malaria transmission season.

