**3.19 Withdrawal Criteria**

Patients will be withdrawn from the study for any one of the following reasons.

- Withdrawal of parental / legal guardian’s consent at any stage.
- Adverse event attributable to the study drug.
- Development of one or more criteria for severe malaria as per WHO definition.
- Development of other severe disease.
- Loss to follow-up.

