**3.22 Sample size calculations**

Assumptions made in the sample size calculations included –

- An intervention that provides at least 30% protection against moderate anaemia will be a useful public heath tool.
- Based on the number of cases of anaemia cases seen at the RVTH and MRC clinic during previous years, it will be possible to recruit 1200 study subjects during the two-year study period.
- 20% of the children will have a PCV of < 20% (moderate anaemia) at the end of the malaria transmission season.
- The attack rate of clinical malaria in children in the control group will be 0.1 episodes per month (a figure based on previous surveys from The Gambia).
- The drop out rate during follow up will be 15%.

A trial with 1200 children enrolled, will have 80% power to detect a 34% reduction in the prevalence of moderate anaemia (PCV<20%) at the end of the malaria transmission season. With a sample size of 1200 children, the study will have 80% power to detect at a 5% level of significance a 32% reduction in incidence of clinical attacks of malaria in children who receive chemoprevention during the surveillance period; 131 episodes of clinical malaria will be expected to occur in the control group followed until the end of one malaria transmission season. The sample size calculation was based on data from previous studies carried out in The Gambia and these studies used haematocrit to determine the presence of anaemia.

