**(d) Time-table**

Timetable

|  | 2003 | | | | | | | | | | | | 2004 | | | | | | | | | | | |
| --- | --- | --- | --- | --- | --- | --- | --- | --- | --- | --- | --- | --- | --- | --- | --- | --- | --- | --- | --- | --- | --- | --- | --- | --- |
|  | 1 | 2 | 3 | 4 | 5 | 6 | 7 | 8 | 9 | 10 | 11 | 12 | 1 | 2 | 3 | 4 | 5 | 6 | 7 | 8 | 9 | 10 | 11 | 12 |
| SCC & ERC submission |  | x | x |  |  |  |  |  |  |  |  |  |  |  |  |  |  |  |  |  |  |  |  |  |
| Enrolment |  |  |  |  |  |  | x | x | x | x | x | x |  |  |  |  |  |  | x | x | x | x | x | x |
| Morbidity surveillance |  |  |  |  |  |  | x | x | x | x | x | x |  |  |  |  |  |  | x | x | x | x | x | x |
| Mortality surveillance |  |  |  |  |  |  | x | x | x | x | x | x |  |  |  |  |  |  | x | x | x | x | x | x |
| Monthly SP treatment |  |  |  |  |  |  | x | x | x | x | x | x |  |  |  |  |  |  | x | x | x | x | x | x |
| End of season survey |  |  |  |  |  |  |  |  |  |  |  | x |  |  |  |  |  |  |  |  |  |  |  | x |
| Dry season visit |  |  |  |  |  |  |  |  |  |  |  |  |  |  |  |  | x |  |  |  |  |  |  |  |

Dose 1 of SP/ placebo

Hb &BF

Monthly SP/placebo at hospital/HC

Passive surveillance, Hb & BF

Clinical assessment

BF & Hb

Clinical assessment, treatment,

± transfusion, Hb & BF

Enrolment, admission

Discharge from Hospital/ HC

Monthly hospital/HC visit

Hospital/HC visit if unwell

Day 7 OPD

visit

End of malaria season

survey

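### Clinic attendance is the only stated route to the primary haemoglobin; no tracing step is written, and nothing says withdrawn children are still measured

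*Protocol*

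**What the plan says.** The primary end-point (section 3.18) is: "Proportion of children with haemoglobin concentration of less than 7g/dL at the end of the malaria transmission season". Section 3.15 says how it is obtained: "Children enrolled in the study will be seen at the OPD clinic at the end of malaria transmission season for examination by a study physician", with a finger-prick for haemoglobin and blood film. The timetable row "End of season survey" is marked for December of each year. No section gives a window, a repeat appointment, tracing or a home measurement for a child who is absent.

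Section 3.19 lists "Loss to follow-up" among the reasons for withdrawal from the study and does not define it. The list also includes withdrawn consent, adverse events attributed to the study drug, severe malaria and other severe disease. It is silent on whether the end-of-season haemoglobin is still taken in these children. Section 3.20 puts the primary analysis on an intention-to-treat basis. Section 3.22 plans for loss: "The drop out rate during follow up will be 15" per cent.

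The protocol also provides the means of reaching families. At entry (section 3.5): "In addition, a detailed address will be obtained". Soon after discharge (section 3.10), "patients will be visited at home by a project field worker". Residence within 30 km is an entry criterion (section 3.4).

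**The concern.** Followed as written, the outcome is never taken in a child who misses the December clinic, and may not be taken in a child withdrawn under section 3.19. An analysis plan cannot recover a blood sample that was not drawn, so this belongs in the protocol.

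Absence may well be related to the outcome. A recovered child's family may see no reason to travel, and a very sick child may be unable to. Severe malaria and other severe disease, as withdrawal reasons, are plausibly linked to low haemoglobin. The analysis called intention-to-treat would then rest on children who attended and were not withdrawn. What is at stake is bias in the primary comparison more than power.

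**Working it through.** **Inputs.** From section 3.22: 1200 children, 20% control prevalence, a 34% reduction, 80% power, 15% drop-out. From section 3.12: 1:1 allocation. The 5% level appears in section 3.22 for the malaria comparison; I take it as two-sided here too. The 20% refers to PCV below 20%, which I carry over to the haemoglobin end-point as the planning value.

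**1. The plan's own figure.** p1 = 0.20; p2 = 0.20 × 0.66 = 0.132; difference 0.068; mean 0.166.
- n = [1.96√(2 × 0.166 × 0.834) + 0.842√(0.2 × 0.8 + 0.132 × 0.868)]² / 0.068² = 469 per arm.
- With continuity correction: (n/4)[1 + √(1 + 4/(n × 0.068))]² = 498 per arm.
- With 15% loss: 498/0.85 = 586 per arm, 1172 in total, within 3% of 1200.

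The sample size is therefore reproduced and already allows for the loss.

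**2. How much is missing.** 0.15 × 600 = 90 per arm, leaving 510. Expected events among those seen: 0.20 × 510 = 102 on placebo and 0.132 × 510 = 67.3 on S/P.

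**3. All-or-nothing bounds.** Count every missing child first as no event, then as an event.
- Placebo: 102/600 = 17.0% to 192/600 = 32.0%.
- S/P: 67.3/600 = 11.2% to 157.3/600 = 26.2%.

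Each range is 15 points wide; the planned difference is 20 − 13.2 = 6.8 points. These are limits, not predictions.

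**4. What attenders would show.** Prevalence among those seen = (p − 0.15q)/0.85, where p is the true prevalence in the arm and q the prevalence among its missing children. Every q is an assumption.

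| True p, placebo / S/P | Missing q, placebo / S/P | Seen, placebo / S/P | Reduction seen |
|---|---|---|---|
| 20% / 13.2% | 20% / 13.2% | 20% / 13.2% | 34% |
| 20% / 13.2% | 40% / 26.4% | 16.5% / 10.9% | 34% (power 74%) |
| 20% / 13.2% | 40% / 13.2% | 16.5% / 13.2% | 20% (power about 31%) |
| 20% / 13.2% | 10% / 26.4% | 21.8% / 10.9% | 50% |
| 20% / 20% | 20% / 40% | 20% / 16.5% | 18% |

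The second row doubles the prevalence among the missing in both arms and leaves the relative effect unchanged. The third hides benefit, the fourth exaggerates it, and the fifth creates an effect where there is none.

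**5. Adding the missing back to the planned result** (102 v 67.3 of 510, risk ratio 0.66, p = 0.0035):
- 20% in both arms: (102 + 18)/600 = 20.0% v (67.3 + 18)/600 = 14.2%; risk ratio 0.71, p = 0.008.
- 15% placebo, 25% S/P: 19.3% v 15.0%; risk ratio 0.78, p = 0.049.
- 10% placebo, 30% S/P: 18.5% v 15.7%; risk ratio 0.85, p = 0.20.

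The last two need selection in opposite directions: missing placebo children better off than attenders (20%), missing S/P children worse off than attenders (13.2%).

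**6. Power.** Without continuity correction, power is 83.2% at 15% missing, 85.3% at 10% and 87.1% at 5%. The gain from tracing is small here.

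**The case against.** The strongest reply is that the point rests on silence. Section 3.15 does not forbid a home measurement, sections 3.20 and 5.0 refer to SOPs that may cover tracing, and section 4.1 mentions a separate analytical plan. Photo cards, recorded addresses, the 30 km limit and project staff at health centres (section 3.14) all help retention. The 15% is drop-out from all causes, so not all 90 per arm are traceable non-attenders; some may have died or withdrawn consent. In a placebo-controlled trial the obvious reasons for staying away act in both arms, and missingness of that kind does little harm to the risk ratio. All of this stands, and it limits the size of the point. It does not supply the missing instruction on how, and in whom, the primary outcome is collected.

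Three stronger readings are tempting and not supported.
- A reader might infer that survey non-attenders are classed as lost to follow-up. No section says so.
- A reader might infer that stopping doses is treated as losing the outcome. Missed doses are not a withdrawal reason in section 3.19. The adherence end-point in section 3.18 presupposes that children who miss doses stay in the trial, and section 3.14 follows subjects through the rainy season.
- A reader might infer that field workers return to the same homes after the survey. Section 3.16 says only "At the end of the dry season study subjects will be visited once"; it names neither place nor staff, and the timetable shows that visit only in May 2004, for the first cohort.

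**Conclusion.** The point holds as a weakness in how the primary outcome is ascertained. It is not a contradiction or a sample-size error. Clinic attendance is the only stated route, no tracing is written, and the protocol does not say that children withdrawn under section 3.19 are still measured, although it claims an intention-to-treat analysis.

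The room for bias is a 15-point range per arm against a 6.8-point planned effect, if the full 15% have no final haemoglobin. The direction is unknown. A material distortion needs the missing to differ from attenders differently in the two arms. The protocol gives no reason to expect that, and no means of ruling it out either. If missingness is similar in both arms, the effect on the result is small. The change should be made because it is cheap and cannot be made after the survey.

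**What to change.** **Section 3.15, add:** Any randomised child who does not attend the OPD survey, including one who has stopped trial medication or met a criterion in section 3.19, will, where consent allows, be visited at home by a project field worker within a fixed window for finger-prick haemoglobin, blood film, questionnaire and vital status.

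**Section 3.19, add:** Apart from withdrawal of consent, these criteria do not end collection of outcomes. Loss to follow-up is recorded only when home tracing at the end-of-season survey has failed.

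This leaves untouched when treatment stops. A home visit cannot supply a haemoglobin for a child who has died, so deaths should be reported by arm beside the primary result.

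**Cost.** 0.15 × 1200 = 180 children over two years, so at most about 90 visits a year if enrolment is even. Field workers would have to take finger-prick samples, a task section 3.10 does not give them, so training and a way of measuring those samples may be needed. Children seen at home would have no physician examination.

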# 3.16 Dry season follow-up

At the end of the dry season study subjects will be visited once. During this visit, a questionnaire will be administered to document morbidity and mortality. Children admitted to

hospital with severe anaemia may be at increased of death if they develop another disease before their haemoglobin has returned to the normal range. Therefore it is important to document the morbidity and mortality pattern in these children over a period of several months after their discharge from hospital.

# 3.17 Surveillance for overall and cause specific mortality

Deaths will be investigated using the post-mortem questionnaire techniques and cause of death established wherever possible.

3.18 Study end-points:

Primary end-points

- Proportion of children with haemoglobin concentration of less than 7g/dL at the end of the malaria transmission season.

#### **Secondary end-points:**

- Proportion of children with anaemia (Hb <11g/dL) and those with severe anaemia (Hb <5 g/dL) at the end of the malaria transmission season.
- Mean Hb concentration at the end of the malaria transmission season.
- Number of OPD attendances with malaria
- Number of hospital admissions with malaria during the surveillance period.
- Number of episodes of severe malaria during the surveillance period.
- Deaths (all-cause and malaria-specific) during the surveillance period.
- Adherence to the study regimen: The number of doses of medication received by children in each group as a proportion of the total number of doses that should have been received.

**3.19 Withdrawal Criteria**

Patients will be withdrawn from the study for any one of the following reasons.

- Withdrawal of parental / legal guardian’s consent at any stage.
- Adverse event attributable to the study drug.
- Development of one or more criteria for severe malaria as per WHO definition.
- Development of other severe disease.
- Loss to follow-up.

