**RESEARCH PROPOSAL**

**1.0 Background to the study**

Anaemia is an important public health problem in sub-Saharan Africa with major social and economic implications. Anaemia causes decreased exercise tolerance and intellectual performance and leads to impairment of normal development. In endemic countries, the prevalence of anaemia in the community is estimated to be 49-89% and that of severe anaemia 1.3-6.4% 1-6. The prevalence of severe anaemia in hospitalised patients is estimated to be in the range of 7-29%7-12. In malaria endemic countries, the incidence of severe anaemia and age specific rates of anaemia correlate strongly with the intensity of *Plasmodium falciparum* malaria transmission, and significant haematological recovery has been seen after malaria control trials13,14. In endemic countries, anaemia has multiple causes such as nutritional deficiencies, infections and haemoglobinopathies. However, *P. falciparum* infection is believed to be a major contributory factor to the aetiology of severe anaemia**.**  Though severe anaemia is an important complication of falciparum malaria, it has not received as much attention from the research community in recent years as cerebral malaria. In areas of seasonaltransmission, cerebral malaria is the dominant form of severe malaria15. In contrast, in areas of high transmission, severe anaemia in young children is the most prevalent form of severe malaria16. Although mortality from severe anaemia, about 10%, is less than that from cerebral malaria (20%-30%), it is likely that several hundred thousand deaths occur from this condition each year.

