#### **3.20 Data management and analysis**

All baseline, surveillance and laboratory data will be collected on forms designed for the trial. Field and laboratory staff will be trained to follow the procedures set out in a series of Standard Operating Procedures (SOPs). Key data will be double entered and inconsistencies checked; range checks will be used for standard variables. Primary analyses will be performed on subjects with intent to treat (ITT) basis.

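### Section 3.19 withdraws children from the study, not only from study drug, on severe illness, and nothing keeps them in follow-up for the endpoints

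*Protocol*

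**What the plan says.** Section 3.19 opens with "Patients will be withdrawn from the study for any one of the following reasons" and lists five reasons. Two are the end of contact in the ordinary sense: consent withdrawn and loss to follow-up. The other three are clinical: an adverse event attributed to study drug, "Development of one or more criteria for severe malaria as per WHO definition", and "Development of other severe disease". The last is not defined. All five carry the same consequence, which is leaving the study.

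The primary endpoint in section 3.18 is "Proportion of children with haemoglobin concentration of less than 7g/dL at the end of the malaria transmission season", measured at the survey in section 3.15. The secondary endpoints include "Number of episodes of severe malaria during the surveillance period", malaria admissions over the same period, OPD attendances with malaria, and "Deaths (all-cause and malaria-specific) during the surveillance period". Section 3.20 states: "Primary analyses will be performed on subjects with intent to treat (ITT) basis". Section 3.15 plans to see enrolled children at season end and makes no exception for those withdrawn. Section 3.16 adds one visit at the end of the dry season and stresses the value of recording illness and death for several months after discharge.

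**The concern.** Two of the withdrawal reasons are severe illness, which is part of what the trial measures. A child who meets one of them during the season leaves before the primary endpoint is measured and before the surveillance period for the secondary endpoints has ended. If S/P prevents severe malaria, this happens more often on placebo. The children lost are also likely to differ from those who remain in their risk of Hb <7 g/dL. The missing data would then depend on both outcome and arm.

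An intention-to-treat label does not cure this. A statistical analysis plan can say how missing values are handled, but it cannot recover haemoglobin values, episodes or deaths that were never collected. The point therefore belongs in the protocol.

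**Working it through.** **1. What is lost and what is not**

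- Triggering severe episode: kept. Section 3.14 has study children admitted to the RVH or MRC hospital fully documented.
- End-of-season Hb (sections 3.15 and 3.18): lost if withdrawal ends contact.
- Repeat severe episodes, later OPD attendances and later admissions: lost.
- Deaths after withdrawal: not secured. Section 3.17 investigates deaths without excluding withdrawn children, but does not say that they are still traced.

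**2. The plan's own sample size (section 3.22)**

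Inputs: control prevalence 20%; 34% reduction, so 0.20 × 0.66 = 13.2%; 80% power; 5% level, taken as two-sided; 15% dropout; 1:1 allocation (section 3.12). Section 3.22 defines moderate anaemia as PCV <20%; I use its 20% as the control rate for Hb <7 g/dL.

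The two-proportion formula with continuity correction gives 498 per arm, 996 in total, and 996 / 0.85 = 1172 enrolled. The plan states 1200, so it reproduces and there is no arithmetic error. Evaluable children are 600 × 0.85 = 510 per arm. Without continuity correction, power at 510 per arm is 83.2%, the reference below.

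**3. Illustration A: a share w of would-be Hb <7 children is withdrawn**

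This is on top of the 15% dropout, and no other children are withdrawn. For true prevalence p, the observed prevalence is p(1 − w) / (1 − pw) and the remaining number is 510(1 − pw). Power uses the pooled normal approximation, two-sided 5%. The shares are assumptions.

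| w placebo | w S/P | Observed placebo | Observed S/P | Observed reduction | Power |
|---|---|---|---|---|---|
| 0 | 0 | 20.0% | 13.2% | 34.0% | 83.2% |
| 10% | 10% | 18.4% | 12.0% | 34.5% | 79.8% |
| 20% | 20% | 16.7% | 10.9% | 34.9% | 75.7% |
| 30% | 30% | 14.9% | 9.6% | 35.4% | 70.7% |
| 20% | 15% | 16.7% | 11.4% | 31.3% | 65.7% |

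Last row in full. Placebo: 0.20 × 0.80 / (1 − 0.04) = 0.1667, with 510 × 0.96 = 489.6 children left. S/P: 0.132 × 0.85 / (1 − 0.0198) = 0.1145, with 510 × 0.9802 = 499.9 left. Reduction: 1 − 0.1145 / 0.1667 = 31.3%.

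**4. Illustration B: direction of the bias**

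Let a share v of each arm be withdrawn, with risk q of Hb <7 g/dL among them. The observed prevalence is (p − vq) / (1 − v). Take v = 2% to 10% on placebo, 32% to 50% lower on S/P, and q = 20% to 80% (all assumptions). Across these, the true 34% reduction appears as 27% to 38%, with power of 42% to 86%. The two extremes of effect both have v = 10% on placebo and q = 80%:

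- v = 5% on S/P: (0.20 − 0.08) / 0.90 = 13.3% against (0.132 − 0.04) / 0.95 = 9.7%, a 27% reduction, power 42%.
- v = 6.8% on S/P: 13.3% against (0.132 − 0.0544) / 0.932 = 8.3%, a 38% reduction, power 69%.

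The apparent effect can therefore move either way.

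**The case against.** The strongest reply is that 3.19 is a generic list of statuses, since it even includes loss to follow-up. Section 3.15 sees enrolled children without exception, section 3.17 investigates deaths without exception, and the analysis plan may say how withdrawn children enter the intention-to-treat analysis. Staff might well have gone on following these children. That is possible, but the text says the opposite for the study as a whole and nothing reconciles the sections. Handling in the analysis can be left to another document; whether the data are collected cannot.

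Several parts of the reply stand, and they limit what can be claimed.

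- A reader might infer that these children leave before any of their events is counted. The triggering admission is documented, so this is not so.
- A reader might use the background statement that "severe anaemia in young children is the most prevalent form of severe malaria" to equate the withdrawal trigger with the primary endpoint. That sentence concerns high-transmission areas. Section 1.0 says cerebral malaria dominates where transmission is seasonal, and section 3.2 describes The Gambia as seasonal. Overlap remains, because section 3.1 calls malaria the most important cause of anaemia among Gambian children, but its extent is not given.
- Children with severe illness are treated and may have recovered by the survey, so not every withdrawn child is a would-be Hb <7 case.
- Larger and more unequal shares would give far worse results. With 60% on placebo and 40% on S/P, illustration A gives an observed reduction of 8% and power of about 6%. That needs about 510 × 0.20 × 0.60 = 61 against 510 × 0.132 × 0.40 = 27 withdrawals, and no figure in the protocol supports it.

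**Conclusion.** The point holds. As written, section 3.19 ends study participation on severe malaria, other severe disease or a drug-attributable adverse event, and no section preserves follow-up. It conflicts with sections 3.15, 3.18 and 3.20. The resulting loss is related to outcome and probably to arm. The 15% dropout allowance covers lost numbers only, not this kind of loss.

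The size is unknown, because the protocol gives no withdrawal rate. With equal shares of 10% to 30%, power falls from 83% to between 80% and 71% and the effect is hardly distorted. A modest imbalance of 20% against 15% brings the observed reduction to about 31% and power to about 66%. These figures rest on the assumed shares, on the plan's 20% and 34%, and on otherwise non-informative dropout.

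Two stronger readings are not supported. One is that the bias must run toward no effect: equal shares slightly enlarge the observed reduction, and the range examined runs from 27% to 38%. The other is that most deaths would go unrecorded: no figure bears on this, and a fatal triggering admission at the RVH or MRC hospital would be documented.

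**What to change.** Reconcile sections 3.15 and 3.17 to 3.20 by separating two things that 3.19 now merges. Any decision about study drug after severe illness or an adverse event stays with the clinicians, and nothing is proposed here about it. Withdrawal from follow-up should be a separate category, limited to a guardian's withdrawal of consent to follow-up or a child who cannot be traced.

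State that every other randomised child stays in follow-up for the end-of-season Hb, malaria and admission counts, and vital status, and is included in the intention-to-treat analysis in the allocated arm. Record the date and reason when study drug is stopped, separately from the date and reason when follow-up ends, so that both can be reported by arm.

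The cost is a wording change and some extra tracing of children who have left study drug. The surveillance, the end-of-season survey and the dry-season visit are already planned. The sample size need not change for this reason.
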